### Process evaluation

A process evaluation will explore the implementation, receipt, and setting of the intervention and help in the interpretation of the outcome results. In trials, where the “same” intervention may be implemented and received in different ways, process evaluations can provide greater explanatory power and understanding of the generalisability of the intervention [18].

### Treatment fidelity

Blinded assessors will be trained to deliver the standardized assessment measures and materials. Health professionals will be registered and will be trained in delivery of the intervention via online training and written materials. Further, health professionals will be supported, where needed, by master trainers while delivering the driving cessation intervention. To monitor fidelity of delivery, participants’ sessions will be detailed in an Excel file by health professionals, e.g. documenting date, topic of session, location, activities, homework, etc. These files will be reviewed by research staff.

### Randomisation and blinding

The research will adopt a single blind design. Further blinding is not feasible given the nature of the intervention. The researcher will generate the random allocation sequence (using simple randomization methods, e.g. sealed envelopes) before baseline assessment is conducted. Clusters, which are matched by the researcher, based on available infrastructure in health and transport in the region, are randomized using concealed allocation to either the intervention or waitlist control group. Clusters will be matched so that pairs of regions are as similar as possible on demographics, population density, and transport and infrastructure, to increase efficiency [16]. Participants will be allocated to either intervention or control condition, based on the area (cluster) that they live in. However, assessors will be blinded to the group assignment of individual participants and will not know which condition the clusters are allocated to. We will ask participants not to inform the independent assessors, if they themselves know, to the best of their ability.

### Procedure

A researcher will have initial telephone contact with potential participants – ie. older adults who self-select for the study. The researcher will answer any questions that potential participants may have and provide further information, and conduct the screening process. A researcher will ask questions of the caller about (as appropriate) their own or the retired/retiring driver’s age, the types of memory problems he or she is having, and their driving situation, to determine their eligibility. Participants with dementia or their family member/support person will be asked to report the individual’s diagnosis of dementia and stage of dementia, ie. participants in the mild to moderate stage dementia will be screened through self-report or proxy-report and the CDR, and will be eligible to participate. If appropriate the researcher will make an appointment for an assessor to attend the participants’ home to conduct baseline assessment. Participants will be given the option to re-consider their participation after their initial contact and before the baseline assessment, or at any time during the study. A follow-up telephone call will be made to potential participants prior to the assessment commencing, by way of reminder, to answer any further questions and confirm their participation.

Initial assessment will take place after obtaining written informed consent. Based on cluster randomisation, participants will be assigned to either the immediate intervention group, or to the wait-list control group. An assessor, who is blind to group allocations will attend in person (e.g. participants’ homes) to conduct all assessments. Following initial assessments, participants will be given a choice of home visit, telephone, or videoconference, for the next two data collection time points (ie. Times 2 and 3, as shown in Fig. 1). The intervention group will receive the intervention approximately two weeks after baseline assessment, and the control group will be offered to receive the intervention after Time 3 assessment. The wait-list control group will receive regular mailed brochures (ie. treatment as usual) and telephone calls throughout the wait period.

### Consent and withdrawal procedures

As outlined above, written informed consent will be obtained from participants at the first meeting, immediately prior to participants’ first assessment. That is, after participants are briefed about the study once again, they will be given the opportunity to ask questions, consider their participation and if they agree, to indicate their agreement by signing the consent form and then proceeding with baseline assessment. Participants’ continued consent and assent will be checked throughout the study. Participants who withdraw from the study will be given the opportunity to also withdraw their data to that point if they wish to. We will collect information about the reasons why participants withdraw from the study.

### Data analysis

Baseline demographic and cluster characteristics will be compared between the intervention and control groups. Data will be analysed using random effects models with maximum likelihood estimation. All analyses will be conducted at the individual and aggregated cluster levels using generalized estimating equations to adjust for clustering effects within geographical location, and adjusting for intracluster correlations between individuals, and according to intention to treat principles.

Hypotheses 1 & 2. Increase in lifespace and the rate of episodes away from home will be analysed at the cluster level using a linear mixed effects model with random intercepts used to analyse the effect of the intervention on number of episodes away from home.

Hypotheses 3 & 4. Testing the effect of the intervention on self-efficacy, wellbeing, depression symptoms, anxiety symptoms, and social isolation, will involve linear mixed effects model.

Qualitative analyses will include thematic analysis of the semi-structured interviews with participants. Coding will be conducted and verified by minimum three members of the research team. The group will convene to review themes until consensus is reached.

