#### Sample size

The sample size calculation for this study used a power analysis applying the mean, and standard deviation (SD), and the minimum detectable difference between populations means = 1, for episodes away from home, obtained from a background study [13]. Allowing for 20% dropout and assuming detectable difference = 1, *SD* = 3.16 and ICC = 0.05. For 80% power with alpha set at 0.05, and the minimum detectable difference between population means, then with an average of 15 dyads per cluster, the minimum number of clusters required is 10. However, more clusters will be included to reach a minimum sample size.

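### The primary hypothesis is given two conflicting analyses (GEE at two levels, and a cluster-level mixed model) with neither named as primary, and both can exceed the 5% error rate at the stated minimum of 10 clusters if used without a small-sample correction

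*Protocol article*

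**What the plan says.** Three sentences in the protocol article, section Data analysis, bear on the primary hypothesis:

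- A general statement: "Data will be analysed using random effects models with maximum likelihood estimation".
- A blanket statement directly after it: "All analyses will be conducted at the individual and aggregated cluster levels using generalized estimating equations", to adjust for clustering by location and for intracluster correlation, under intention to treat.
- A specific statement for Hypotheses 1 and 2: lifespace and the rate of episodes away from home "will be analysed at the cluster level using a linear mixed effects model with random intercepts".

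Hypotheses 3 and 4 are also given a linear mixed effects model. No sentence says which analysis decides the trial.

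The section Sample size sets the scale: "with an average of 15 dyads per cluster, the minimum number of clusters required is 10". It adds that more clusters will be included, without giving a number. The sections Design and Randomisation and blinding say that clusters are matched in pairs; Data analysis does not mention the pairs.

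**The concern.** GEE and a linear mixed model are alternative ways to handle clustering. GEE estimates a marginal effect with a sandwich variance; the mixed model uses a likelihood with a between-cluster variance component. Each gives its own standard error and p-value, and an individual-level fit can differ again from a cluster-level one. If all analyses are by GEE, the primary outcomes cannot also be analysed by a mixed model unless one of the two is subordinate, and the text does not say which.

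Two things are at stake. First, the deciding analysis could be picked after the results are seen. Second, both named methods rely by default on having many clusters. The uncorrected sandwich variance is biased downwards when clusters are few, and maximum likelihood (unlike REML) underestimates the between-cluster variance. At 10 clusters either can make the test too liberal and the interval too narrow.

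**Working it through.** **1. The sentences side by side**

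| Sentence | Framework | Level |
|---|---|---|
| General | random effects, maximum likelihood | not stated |
| Blanket, all analyses | GEE | individual and aggregated cluster |
| Hypotheses 1 and 2 | linear mixed model, random intercepts | cluster only |

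The first and third agree, because a mixed model with random intercepts is a random effects model and can be fitted by maximum likelihood. The second conflicts with them on framework, and with the third on level.

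**2. Inputs (Sample size section)**

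SD 3.16, ICC 0.05, difference 1, alpha 0.05 (taken as two-sided), power 80%, 15 dyads per cluster, 20% dropout (15 × 0.8 = 12 analysed), minimum 10 clusters.

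**3. The plan's figure of 10 clusters**

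It does not reproduce from these inputs. The usual two-arm formula gives 2 × (1.96 + 0.842)² × 3.16² / 1² ≈ 157 per arm.

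- m = 15: design effect 1 + 14 × 0.05 = 1.70. 157 × 1.70 ≈ 267 per arm, and 2 × 267 / 15 = 35.6, so 36 clusters in total.
- m = 12: design effect 1.55, and 2 × 157 × 1.55 / 12 = 40.6 clusters.

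That is a separate matter. It is used here only to choose 36 as a larger cluster number, next to 10 and 20.

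**4. GEE with an uncorrected sandwich variance: closed form**

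Take K equal clusters, half per arm, and let SSB be the between-cluster sum of squares within arms. The sandwich variance of the arm difference uses SSB/K where the unbiased estimate uses SSB/(K − 2). Rejecting at 1.96 is therefore the same as rejecting a t statistic on K − 2 df at 1.96 × √((K − 2)/K):

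- K = 10: 1.96 × √(8/10) = 1.753, and P(|t₈| > 1.753) = 11.8%.
- K = 20: 1.96 × √(18/20) = 1.859, and P(|t₁₈| > 1.859) = 7.9%.
- K = 36: 1.96 × √(34/36) = 1.905, and P(|t₃₄| > 1.905) = 6.5%.

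The ICC cancels, so the figure is the same at any ICC. The same result holds for maximum likelihood applied to one mean per cluster with a z test, which is one literal reading of the sentence for Hypotheses 1 and 2.

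**5. Maximum likelihood on individual data: simulation**

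The variance per cluster is SSB/K when that is at least SSW/(K(m − 1)), where SSW is the within-cluster sum of squares. Otherwise it is the pooled value (SSB + SSW)/(Km). The test is a Wald z at 1.96. Type I error at nominal 5%, with ICC 0.05, no pairing effect and 200,000 null trials per setting (ranges are m = 12 to 15):

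| Clusters | GEE, z | ML, z | t test on cluster means |
|---|---|---|---|
| 10 | 11.8% | 8.7–9.1% | 5.0% |
| 20 | 8.1% | 7.3–7.6% | 5.1% |
| 36 | 6.6% | 6.4–6.5% | 5.0–5.1% |

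Repeat runs at m = 12 gave ML 8.6% at 10 clusters and 7.2% at 20. The ML figure depends on the ICC: at 10 clusters it is 4.7–4.8% at ICC 0, 5.7–6.0% at 0.01 and 10.5–10.9% at 0.10. A smaller check with unequal cluster sizes at 10 clusters (800 fits, ICC 0.05) gave GEE 16.5% and ML 8.8%.

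**6. Effect of the matching**

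The documents give no figure for how much between-cluster variance the pairs explain. Assume a share, keep the total ICC at 0.05 and m at 12, and ignore the pairs in the analysis:

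| Clusters | Share explained | GEE, z | ML, z |
|---|---|---|---|
| 10 | 0 | 11.8% | 8.6% |
| 10 | 50% | 8.8% | 5.8–5.9% |
| 10 | 80% | 7.1% | 4.2% |
| 20 | 50% | 5.4% | 4.7% |
| 36 | 50% | 4.2% | 4.0% |

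Baseline adjustment and repeated measurements were not modelled.

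**The case against.** The strongest reply concerns the error rates. The article names no test statistic, degrees of freedom or variance correction. Such detail is commonly left to an analysis plan, which is not shown. Maximum likelihood or GEE with a suitable correction would not contradict the text. The simulated excess also assumes that matching explains nothing, and 10 clusters is a floor that the plan intends to exceed. All of this stands. It makes the error-rate figures conditional, and with effective matching and 20 or more clusters the excess can disappear.

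Three stronger readings are tempting, and the documents do not support them:

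- A reader might count three incompatible analyses. The maximum-likelihood sentence and the mixed-model sentence are compatible, so the conflict is between two frameworks and two levels.
- A reader might conclude that the 5% level is not held. That follows only for uncorrected large-sample inference, which the article does not state.
- A reader might take the unspecified random intercepts to be for participants only, leaving cluster out of the model. The same section says that analyses adjust for clustering by location and for intracluster correlation, so this reading contradicts the text.

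None of this removes the conflict itself. An analysis plan can add detail, but it cannot make GEE the method for all analyses and also make a mixed model the analysis of the primary outcomes without subordinating one of them.

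**Conclusion.** The concern holds in a limited form. The stated text gives the primary hypothesis two conflicting frameworks and two levels and designates neither, so several p-values are available for one question. This does not depend on any calculation.

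The calculation shows that the choice is not neutral. With uncorrected Wald inference at the stated minimum of 10 clusters, type I error is about 12% for GEE and 8.5–9% for maximum likelihood, against 5% for a t test on cluster means. At 20 clusters it is about 8% and 7%, and at 36 about 6.5% for both. These figures assume ICC 0.05, 12 analysed per cluster (the ML range and the cluster-mean figures also cover 15), equal cluster sizes, one follow-up, and pairing absent from both data and analysis. If pairing explained half the between-cluster variance, the figures at 10 clusters would be about 9% and 6%.

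**What to change.** Name one primary analysis, one level and one treatment contrast. Either of these would serve:

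- an individual-level linear mixed model fitted by REML, with small-sample degrees of freedom (Kenward-Roger or Satterthwaite), accounting for cluster and for the matched pairs; or
- a t test on cluster summaries, paired if the pairs are kept in the analysis.

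Replace the maximum-likelihood wording to match. Remove the blanket GEE sentence, or make GEE a sensitivity analysis with a small-sample variance correction (Kauermann-Carroll or Mancl-DeRouen) and t degrees of freedom.

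The change is to wording only, but it has a statistical price when clusters are few. At 10 clusters with no pairing effect, REML with t on 8 df gives intervals about 36% wider than uncorrected GEE and 28% wider than ML with a Wald z. It is also conservative: it rejects 3.4–3.7% of the time under the null, or about 2% if pairing explains half the variance and the model ignores it. This is why the pairs belong in the model. A paired t test on 10 clusters has 10/2 − 1 = 4 df, so that gain also has a cost. Both costs shrink as clusters are added.

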## Methods

### Design

A cluster randomized controlled trial will be conducted with regions (electoral districts) used as the unit of randomisation, to minimize the risk of contamination between conditions. Cluster randomisation aims to also address possible attrition, as participants will not be made aware of an alternative group. Clusters will be matched so that pairs of regions are as similar as possible on demographics, and potential local area transport and health infrastructure, to increase efficiency [16]. Clusters will be randomized using concealed allocation to either the intervention or waitlist control group. Randomisation to treatment or wait-list control condition will occur before baseline measurement. During a period of baseline data collection, no cluster will be exposed to the intervention. After baseline, one will proceed to the intervention arm, while the other will proceed to the wait-list ‘treatment as usual’ (ie. no intervention, written information, pamphlets) control arm – to receive the intervention at a later time (after Time 3, see Fig. 1).

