##### Secondary outcome measures

‘Safe transport status’ is the major secondary outcome measure. We will collect information from participants about the mode of transport used for each episode away from home (e.g. walk, taxi, bus), counted for the previous week, and about any concerns they had about the mode of transport used (e.g. safety). Other secondary outcome measures include wellbeing, depression, anxiety, self-efficacy and self-performance and isolation, which will be collected from dyads; as well as caregiving strain collected from carer/family member only (see Table 2). At baseline, general questions related to demographics, mobility, proximity to services, usual transport used, community involvement, socioeconomic status, and the circumstances surrounding driving cessation (e.g. participant is the only driver in household, participant’s readiness to transition to retired driver), will be collected.

**Table 2 Tab2:** Pre- and post-intervention measurement tools relating to persons with dementia and family members/care partners, collected at Times 1, 2, and 3

Person with dementia	Family Member	Measure
Lifespace; Episodes away from home	Lifespace; Episodes away from home	Lifespace metrics via Smartphone GPS data; Self-report, Life Space Questionnaire [19]
Mode/s of transport used in previous week	Mode/s of transport used in previous week	Semi-structured Interview
Readiness for transitioning to non-driver		Assessment of Readiness for Mobility Transition [20]
Social Isolation	Social Isolation	Loneliness Scale [21]
Wellbeing/Quality of life	Wellbeing/Quality of life	Personal Wellbeing Index [22]
	Caregiver Strain	Caregiver Burden Index [23]
Self-efficacy - Transport and lifestyle	Caregivers Self-efficacy	Transport and Lifestyle Self Efficacy [13]
Depression and Anxiety symptoms	Depression and Anxiety symptoms	Geriatric Depression Scale [24]; Geriatric Anxiety Inventory [25]
Individualized goal setting (and achievement of goals)	(completed together)	Canadian Occupational Performance Measure [26]
Perceptions of needs and experiences, feedback	Perceptions of needs and experiences, feedback	Semi-structured interviews with sub-sample

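### The stated primary analysis does not make the Time 1 outcome a covariate and does not say what becomes of the matched pairs; adjusting for baseline is the near-free gain, the pair term a conditional one

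*Protocol article*

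**What the plan says.** All references are to the protocol article.

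- **Primary model (Data analysis).** "Increase in lifespace and the rate of episodes away from home will be analysed at the cluster level using a linear mixed effects model". The intercepts are random. The general paragraph of that section names adjustment for clustering by location and for correlation between individuals within a cluster, and no other.
- **Baseline (Data analysis; Table 2).** "Baseline demographic and cluster characteristics will be compared between the intervention and control groups". That sentence concerns demographic and cluster characteristics, not the Time 1 outcome. Table 2 lists lifespace and episodes away from home among the measures "collected at Times 1, 2, and 3".
- **Pairs (Design; Randomisation and blinding).** "Clusters will be matched so that pairs of regions are as similar as possible on demographics". Both sections give efficiency as the purpose, and Design sends one region to each arm.
- **Order of events (Design; Recruitment).** Clusters are randomised before baseline measurement. Participants are recruited on a rolling basis over 2.5 years.
- **Sample size.** Difference of 1 episode, SD "3.16 and ICC = 0.05", 20% dropout, 80% power, 15 dyads per cluster. No baseline correlation or within-pair correlation is used.

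**The concern.** Two sources of precision are built into the design, and the stated analysis commits to neither.

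The first is the Time 1 outcome. If it is not a covariate, the treatment contrast carries more between-person variance than it needs to. Any difference in baseline mobility between arms also passes into the estimate, wholly or in part. Such a difference is plausible here: clusters are few, and people enter after their region's allocation is fixed. Blinding is stated for assessors; the text does not say whether those who recruit and screen are blinded. Comparing baseline characteristics between arms describes an imbalance but does not correct it.

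The second is the matching. Pairing sharpens inference only if the analysis uses it. If the pairs resemble each other and the analysis ignores them, the standard errors are too large and the test is conservative.

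**Working it through.** **Inputs from the Sample size section.** Difference 1, SD 3.16, ICC 0.05, alpha 0.05 (two-sided assumed), power 80%, m = 15 dyads per cluster, or 15 × 0.8 = 12 after dropout.

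**Inputs assumed.** Baseline-to-follow-up correlation r = 0.3, 0.5, 0.7; correlation ρ of true cluster means within a pair, 0 to 1. The article gives neither.

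**1. The plan's own figure.**
- Individual randomisation: n per arm = 2 × 7.849 × 3.16² / 1² = 156.8.
- m = 15: design effect 1 + 14 × 0.05 = 1.70; 156.8 × 1.70 = 266.5 per arm; / 15 = 17.8, so 18 clusters per arm, 36 in total.
- m = 12: design effect 1.55; 243.0 per arm; / 12 = 20.2, so 21 per arm, 42 in total.

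The stated minimum of 10 clusters is not reproduced, whether read as a total or per arm. With m = 15, ten in total give about 32% power and ten per arm about 56% (normal approximation). That is a separate matter. It is used here only to show that precision is scarce.

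**2. Baseline as covariate.** In units of the follow-up variance, and taking the same r within and between clusters:
- follow-up only: 1
- change score: 2(1 − r)
- covariate adjustment: 1 − r²
- adjustment relative to change score: (1 − r²) / [2(1 − r)] = (1 + r)/2

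| r | change score | covariate | covariate vs follow-up only | covariate vs change score |
|---|---|---|---|---|
| 0.3 | 1.40 | 0.91 | 0.91 | 0.65 |
| 0.5 | 1.00 | 0.75 | 0.75 | 0.75 |
| 0.7 | 0.60 | 0.51 | 0.51 | 0.85 |

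A repeated-measures model with Time 1 as an outcome and arms free to differ there estimates the effect as a difference in change, so the last column applies to it as well. A model with baseline constrained equal already has the benefit.

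Relative to follow-up only, the clusters needed at m = 15 fall from 36 to 34, 28 or 20 at r = 0.3, 0.5 or 0.7. For example, at r = 0.5, 17.77 × 0.75 = 13.3, so 14 per arm and 28 in total. At m = 12 they fall from 42 to 38, 32 or 22.

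**3. Pairs.** The variance of a cluster mean, in units of SD², is 0.05 + 0.95/m. Pairing multiplies the between-cluster part by (1 − ρ). At m = 15 and ρ = 0.5 the ratio is (0.025 + 0.0633) / (0.05 + 0.0633) = 0.78. A paired t-test on k pairs has k − 1 degrees of freedom against 2k − 2 unpaired, so 4 against 8 with 5 pairs.

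| pairs | m | paired power at ρ = 0 / 0.5 / 1 | unpaired power, no pair correlation | break-even ρ |
|---|---|---|---|---|
| 5 | 15 | 21% / 25% / 33% | 26% | 0.53 |
| 5 | 12 | 19% / 22% / 28% | 23% | 0.60 |
| 10 | 15 | 47% / 57% / 71% | 51% | 0.25 |
| 10 | 12 | 42% / 50% / 61% | 46% | 0.28 |

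The break-even is against an unpaired test on unmatched clusters. A simulation of 40,000 trials (m = 12) ran both tests on the same matched data:
- 5 pairs, ρ = 0.5: power 22.6% paired, 21.6% unpaired; at ρ = 0, 19.4% and 23.4%. On this comparison the break-even is somewhat below one half.
- 20 pairs, ρ = 0.5: 83.8% and 79.8%.
- No true effect, ρ = 0.5: the test that ignores pairs rejects in 3.3% (5 pairs) or 3.1% (20 pairs) of trials, instead of 5%.

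**The case against.** **Silence is not exclusion.** The article gives no covariate list, and one may stand in an analysis plan that is not shown. This stands. A reader might infer that baseline is left out altogether, and the text does not support that. The hypothesis is worded as an increase in lifespace, and a random-intercept model is fitted to an outcome measured three times, so Time 1 may enter as a change score or as the first repeated measure. What remains is that the article does name its adjustments and this one is not among them, while every candidate reading is matched or improved on by covariate adjustment.

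**Matching may bring no gain.** A reader might infer that the plan throws away precision the matching has already secured. That is not supported either. No within-pair correlation is given, and if the minimum of 10 clusters is a total there are 5 pairs, where a strict paired analysis can lose power. Breaking the match is then a legitimate choice. The 4-point gain needs 20 pairs, a number found nowhere in the article, although it does say that more clusters than the minimum will be included.

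**Baseline tests.** A reader might infer that significance tests of baseline characteristics are planned. The text says only that they will be compared, so there is nothing to object to.

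**The correlations are assumed.** True, and the formulas also take one r within and between clusters. The size of the gain is therefore uncertain; its direction is not.

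**Conclusion.** The concern holds in limited form. The stated adjustment covers clustering only. The role of the Time 1 outcome is not fixed, and the pairs adopted for efficiency are not carried into the analysis or expressly set aside.

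The baseline half carries the weight. Adjustment reduces variance by 9%, 25% or 49% against follow-up only, and by 35%, 25% or 15% against change scores, at r = 0.3, 0.5 or 0.7. It also corrects imbalance in the measured Time 1 outcome, but cannot correct selection on what was not measured. If the intended model already constrains baseline equal between arms, only the wording is lacking.

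The pair half is secondary. Ignoring effective pairs makes the test conservative, not invalid. With 5 pairs a strict paired analysis gains only if the within-pair correlation exceeds about 0.5 to 0.6, measured against an unpaired test on unmatched clusters. With 10 pairs the threshold is about 0.25 to 0.28.

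**What to change.** 1. **Primary model.** State that Times 2 and 3 are the outcomes in the mixed model, with the participant's Time 1 value of the same outcome as a covariate. Equivalently, keep all three times as outcomes with baseline constrained equal between arms.
2. **Pairs (secondary).** If about 10 or more pairs are randomised, include the matched pair as a random effect with small-sample degrees of freedom. With fewer, state in advance that the match is broken in the analysis, and why.

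Both are changes of wording, to be made before outcome data are seen. No new data are needed, since Time 1 is already collected. The price is a few cluster-level degrees of freedom for the pair term, which is why it is tied to the number of pairs.
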